**Methods:**

This is a protocol for a randomized controlled trial with blind evaluation. Ninety-six ICU patients will be recruited from a single center and randomly assigned to a control group or an intervention group. To determine the level of protocol activity the patient will receive, the patients’ ability to participate actively and their muscle strength will be considered. The protocol consists of five phases, ranging from passive therapies to walking and climbing stairs. The primary outcome will be the functional status at ICU discharge, measured with the Barthel Index and the ICU Mobility Scale (IMS). Measured secondary outcomes will include the level of physical activity, maximal inspiratory and expiratory pressures, forced expiratory volume in 1 second, maximum voluntary ventilation, handgrip strength, surface electromyography of the lower limb muscles, and results of the Timed Up and Go and 2-Minute Walk tests. Evaluations will be made within 2 days of ICU discharge except for the level of activity, which will be evaluated daily. Physiological variables and activity level will be analyzed by chi-square and *t* tests, according to the intention-to-treat paradigm.

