#### Patient assessment procedures

At the time of admission to the ICU and up to 2 days after admission, the patient will be examined against the inclusion criteria. The patient’s functionality in the 2 weeks before admission will be evaluated with the Barthel Index, which will be assessed by directly questioning the patient or their caregiver if they are unable to respond. Evaluation will include hemodynamic, respiratory, and cardiac stability for the safe practice of early mobility, and the absence of exclusion criteria will also be assessed. The patient will then be randomly placed in the control group or the intervention group.

After the patient is enrolled in the study, the initial variables will be collected, consisting of data related to the patient and their hospitalized and pre-hospitalization levels of functionality. At that time, an accelerometer will be placed on the patient to monitor their level of physical activity during the entire stay in the ICU.

Data on the patient’s hospitalization and the evolution of their condition, as well as the level of physical activity performed, will be collected during the entire stay in the hospital.

Upon discharge from the ICU or within 2 days of discharge, all patients will undergo a complete evaluation of their respiratory, muscular, and functional systems through methods already described in the academic literature and performed by a blind evaluator. The accelerometer will be removed, and the data will be analyzed in a dedicated computer program. Figure 2 shows a flowchart presenting the methods used in the study.

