The muscular evaluation will be performed by measuring MS with a handgrip dynamometer (Jamar Enterprises LDT®, Hoddesdon, United Kingdom) [26]. Muscle activity will be measured by electromyography of three muscles in the lower limbs—the anterior tibial, medial gastrocnemius, and vastus lateralis muscles—using a Miotool Miotec device (Miotec Equipamentos Biomédicos Ltda®, Porto Alegre, Brazil). The patient will perform the voluntary contraction three times in each muscle, accompanied by an electrogoniometer (Miotec Equipamentos Biomédicos Ltda®, Porto Alegre, Brazil) [27, 28].

Muscular function and mobility will be evaluated using the Timed Up and Go test [29] and the 2-Minute Walk test [30].

Functionality will be evaluated using the Barthel Index [31], measured by directly questioning the patient and by using the ICU Mobility Scale (IMS) [32].

The demographic data and initial evaluation of the patient will be collected on a data sheet. The patient’s physical activity data will be collected by the accelerometer and stored in the equipment’s software, and will later be included in the general tabulation of patient data. The physical evaluation data (dynamometry, electromyography, respiratory MS, and spirometry) will be collected on the same data sheet.

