### Statistical analysis including sample size calculations

Analyses for all aims will be performed according to the intention-to-treat paradigm. Comparative analysis between the control group and the intervention group will be performed for all outcome variables. For the comparison of the physiological variables and the levels of activity between the groups, a statistical test will be used to compare the two independent groups. For parametric data, the *t* test will be used.

To calculate the sample size for the primary outcome, we based the design on results found in Schweickert (2009) for a clinical trial. To an estimated expected difference in means in the primary outcome (Barthel Index score) of 13 points and a standard deviation of 22 points. Considering a statistical power of 80% and an alpha error of 0.5, we found that the number of subjects should be 48 per group, totaling 96 patients in the study.

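### Timed Up and Go gives no time for patients who cannot walk at ICU discharge, so comparing mean times would cover walkers only and would probably dilute a real benefit

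*Protocol article*

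**What the plan says.** The abstract lists "results of the Timed Up and Go and 2-Minute Walk tests" among the secondary outcomes. Under Patient assessment procedures, at ICU discharge or within 2 days of it, "all patients will undergo a complete evaluation of their respiratory, muscular, and functional systems". The same section states that "Muscular function and mobility will be evaluated using the Timed Up and Go test" and the 2-Minute Walk.

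Under Statistical analysis including sample size calculations, "Analyses for all aims will be performed according to the intention-to-treat paradigm" and "Comparative analysis between the control group and the intervention group will be performed for all outcome variables". The only test named there is conditional: "For parametric data, the *t* test will be used". The abstract adds the chi-square test: "Physiological variables and activity level will be analyzed by chi-square and *t* tests".

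On who is enrolled, Level I of the programme is for patients who do not respond to commands, and Level II is for those with a Medical Research Council strength score below 3 in the hip muscles. The exclusions under Participants include death before the final evaluation but not inability to walk.

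**The concern.** Timed Up and Go yields a number of seconds only if the patient gets up and walks. The article keeps non-walkers in the study, promises to evaluate them and promises to analyse everyone as randomised, yet for these patients there is nothing to average. Without an assigned value or rank, a comparison of mean seconds covers only those who could do the test.

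That subset is not protected by randomisation. Walking is one of the abilities the programme trains, and it separates the upper levels from the lower ones. If the programme works, some weaker intervention patients become able to take the test and enter with slow times, while similar controls contribute nothing. The intervention mean is pulled towards worse values by the very patients who benefited. At stake are an understated effect and lost power on a secondary outcome.

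**Working it through.** **Inputs from the article.** 48 patients per group; expected difference 13 points and SD 22 on the Barthel Index; power 80%. Alpha is printed as 0.5; the calculation below uses 0.05 two-sided, which comes close to 48, whereas 0.5 two-sided gives 14 per group.

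**Reproducing the article's figure.** d = 13/22 = 0.591. The normal formula gives n = 2 × (22 × (1.960 + 0.842)/13)² = 44.96, so 45 per group. The exact t-test solution is 45.94, so 46, within 2 of the stated 48. With 48 per group the t test has 81.7% power. This sizing concerns the Barthel Index; the article gives no figure for Timed Up and Go.

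**Assumptions for the illustration.** Mobility is a latent normal score with SD 1 and mean 0 in controls and 0.591 in the intervention group, higher being better. A patient below a threshold c cannot walk and has no time. The threshold is set so that a share p of controls is unable. The article gives no p. Its Background reports peripheral weakness in 25–33% of patients ventilated for 4 to 7 days and in 60% of those with respiratory failure. These are not walking rates, but they make a negligible share unlikely, so p is varied from 10% to 50%.

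**Effect among walkers, closed form.** With φ and Φ the standard normal density and distribution function:
- control mean among walkers = φ(c)/(1 − p);
- intervention mean among walkers = d + φ(c − d)/(1 − Φ(c − d)).

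For p = 20%, c = −0.842. The control mean is 0.350, the intervention mean 0.746 and the difference 0.396 SD, which is 67% of 0.591. The same steps give 0.341 SD for p = 30% and 0.296 SD for p = 40%.

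**Power by simulation** (48 per group, 3,000 trials per row, so each power figure is good to about ±2 points). The t test uses walkers only; the rank test uses everyone, with those unable tied at worst.

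| Controls unable | Intervention unable | Difference among walkers (SD) | Power, walkers only | Power, worst rank |
|---|---|---|---|---|
| 10% | 3% | 0.47 | 69% | 80% |
| 20% | 7% | 0.40 | 59% | 80% |
| 30% | 13% | 0.34 | 49% | 79% |
| 40% | 20% | 0.29 | 38% | 77% |
| 50% | 28% | 0.25 | 29% | 76% |

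If every patient had a value, power would be about 82%.

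**Two other scenarios.**
- *No effect, 30% unable in both groups:* the difference among walkers is −0.003 SD, and the t test rejects in 2.6% + 2.4% = 5.0% of trials. There is no bias.
- *Benefit of 0.59 SD only in patients who would otherwise be unable, 20% to 40% unable:* the difference among walkers is −0.12 to −0.14 SD. It is significant in the wrong direction in 10% to 15% of trials and in favour of the programme in at most 0.3%. The worst-rank test favours the programme in 6% to 21%; a t test with every value observed would be significant in 10% to 26%.

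**The case against.** The strongest objection is that this rests on silence. Nowhere does the article say that non-walkers are dropped, and the scoring of an inability could sit in a full protocol or analysis plan that is not shown. That is correct: a walkers-only analysis is what follows if nothing is added, not a rule the article states. The point still merits action, because the article pairs a universal intention-to-treat claim with an outcome that has no value for some patients. The remedy also depends on what is recorded at discharge, and recruitment is already under way.

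A reader might infer that the article prescribes a t test for both walking tests. It does not. The t test is conditional on parametric data, and the sentence before it refers to physiological variables and activity levels. Its use for Timed Up and Go is an inference from its being the only test named for continuous data.

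A reader might also infer that both tests lose non-walkers. Only Timed Up and Go does. The 2-Minute Walk is a distance, so a non-walker can score 0 m and stay in; there the difficulty is a cluster at zero, which makes a t test doubtful.

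Entry at Level I or II does not show that a patient cannot walk at discharge. Patients are reassessed daily and progress, and all had a Barthel Index of 100 before admission. The article neither gives the share still unable nor assures that it is zero.

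Finally, both primary scales, the Barthel Index and the ICU Mobility Scale, can score a non-walker, so restored walking is captured in the primary result. This stands and limits the consequence.

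**Conclusion.** The point holds for Timed Up and Go as a secondary outcome. As written, the evaluation of all patients and the intention-to-treat comparison cannot both be met by a comparison of mean times, because patients unable to walk have none. The likely consequence is dilution of a real benefit: under the illustration, from 0.59 SD to about 0.40 to 0.29 SD, with power falling from about 82% to 59% to 38% when 20% to 40% of controls are unable.

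These figures rest on an assumed share unable to walk, an effect size borrowed from the Barthel Index, a uniform normal shift and a sharp threshold. They show the direction and possible scale; they do not predict this trial. The stronger claim that the analysis will hide benefit is not supported: the loss depends on the unknown share, and there is no bias when there is no effect. The primary outcome is unaffected. This should be changed, but it does not undermine the trial.

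**What to change.** - On the discharge assessment form, record 'unable to perform' for physical reasons separately from 'not done' for any other reason, for each test.
- For Timed Up and Go, give patients unable for physical reasons the worst rank and compare all assessed randomised patients with the Wilcoxon-Mann-Whitney test.
- For the 2-Minute Walk, score non-walkers 0 m and use the same rank test because of the cluster at zero.
- Report the proportion able to perform each test by arm, and give completers' times as descriptive only.

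The cost is one tick box per test and a few sentences of analysis wording. The downside is that the Timed Up and Go effect becomes a rank comparison rather than a mean difference in seconds. Because recruitment has started, the form should change soon, and inability in patients already assessed should be recovered from source notes where possible. The change does not address the exclusion of patients who die before the final evaluation, a separate departure from intention to treat.

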#### Follow-up for outcome assessment

A longer-term follow-up will be performed for functional status by the Barthel Index. This scale will be reapplied at the time of hospital discharge, after 3 months and 1 year of hospital discharge. At these times the Barthel Index will be re-evaluated by phone contact.

### Primary and secondary outcome measures and assessment points

The outcome variables of the study will be respiratory, muscular, and functional variables; the length of stay in the ICU; and analyzed variables of physical activity, measured by the accelerometer.

The primary outcome will be the functional status at discharge from the ICU. The functional status is the difference between baseline and final score on both the Barthel Index and the IMS. Therefore, at discharge from the ICU, the Barthel Index and IMS will be redone, and the quantitative final score on those scales will be considered as the primary endpoints of the study. The secondary outcomes will be the respiratory and muscular variables and the number of days of hospitalization in the ICU. Further secondary outcomes will be the variables of physical activity performed during this period, which include an analysis of the intensity levels of the exercise to which the patient was submitted and the percentage of time spent sitting, lying, and standing.

For both groups, the occurrence of any adverse events related to motor therapy, such as respiratory or hemodynamic instability, accidental removal of invasive devices, falls, or pain will be recorded. Figure 3 illustrates the schedule of enrollment, allocation, intervention, and assessment of the study.

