### Participants

Participants will be patients admitted to the ICU who are 18 years old or older with a Barthel Index equal to 100 points before hospitalization, who have not been transferred from another hospital, and who meet the criteria for inclusion in the progressive mobilization program will be enrolled in the study. The criteria for for initiation and continuity the progressive mobilization program follow the safety consensus described in the academic literature [19] and some points are as follows: respiratory rate (RR) ≤ 35 breaths per min, absence of cardiac arrhythmias or acute ischemia, heart rate (HR) between 50 and 140 beats per min, without the use of vasoactive drugs or without dose increase, mean arterial pressure (MAP) between 60 and 120 mmHg, absence of active bleeding, and no prescription of bed rest. Patients with MV with inspired fraction of inspired oxygen (FiO_2_) ≤ 60% and positive end-expiratory pressure (PEEP) ≤ 10 cmH_2_O are also eligible to participate.

Patients to be excluded include patients with neurological diagnoses associated with motor alterations, who refuse to carry out the proposed exercises or ask to withdraw less than 3 days after beginning the protocol, with contraindications for movement, those with pre-existing amputations or who undergo amputation upon hospitalization, and those who die before the final evaluation will be excluded from the study.

After admission to the ICU, patients will be evaluated at all times of the day regarding the inclusion criteria in the program. Patients will be evaluated within 2 days of admission to the ICU to participate in the study. If they do not present the criteria for initiating a mobilization program in that period [19], they will not be randomized and will not be included in the study.

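### The primary outcome is defined both as change from baseline and as score at ICU discharge, which leaves the IMS endpoint open; the Barthel comparison is unaffected

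*Protocol article*

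**What the plan says.** Under Primary and secondary outcome measures and assessment points, the article states: "The functional status is the difference between baseline and final score on both the Barthel Index and the IMS". The sentence that follows, introduced as a consequence of the first, says that "at discharge from the ICU, the Barthel Index and IMS will be redone" and that "the quantitative final score on those scales will be considered as the primary endpoints of the study". One sentence names a difference, the next a level.

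Two other places bear on baseline values:
- Participants admits only patients "with a Barthel Index equal to 100 points before hospitalization". Patient assessment procedures adds: "The patient’s functionality in the 2 weeks before admission will be evaluated with the Barthel Index".
- The same section describes the initial variables as "consisting of data related to the patient and their hospitalized and pre-hospitalization levels of functionality". No IMS reading is named there. A baseline IMS is implied only by the statement that the scale is repeated at discharge, and the text does not say when it is taken.

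Elsewhere the outcome reads as a level. The abstract's Methods paragraph and the Aim section both speak of functional status at ICU discharge, without mention of change.

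On analysis, Statistical analysis including sample size calculations promises a between-group comparison of all outcome variables. The only method it then gives is a test for unpaired groups, in a sentence that begins "For the comparison of the physiological variables and the levels of activity between the groups, a statistical test will be used to compare the two"; a t test is named for parametric data. No baseline covariate is named.

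**The concern.** A primary endpoint should be one variable per scale. Here the IMS has two, and someone writing the analysis plan could not tell from this section which sentence governs.

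The choice matters for the IMS because baseline status at enrolment may vary widely. Ventilated patients are eligible, and the mobilization program takes patients from those who do not respond to commands (Level I) to those with muscle strength of 3 or more (Level III). If baseline IMS is recorded at enrolment, change and discharge score will give different estimates in any one data set. Both could be defended from the protocol's own words after the data are seen.

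**Working it through.** **1. The plan's own figure.** Inputs from the sample-size paragraph: difference 13 Barthel points, SD 22, power 80%, 1:1 allocation. I take alpha as two-sided 0.05. The printed 0.5 gives only 14 per group and is a separate matter.

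n per group = 2 × [22 × (1.960 + 0.842) / 13]² = 44.96, so 45; the exact t test gives 45.94, so 46. The plan states 48. At 48 per group, power is 82.5% (normal) or 81.7% (t). The plan's figure is adequate and rests on the Barthel Index alone.

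**2. Barthel Index.** Baseline is 100 for every participant, so change = final − 100. Subtracting a constant alters neither the difference in means nor the SD, so the t statistic and p-value are identical under both definitions. There is also no baseline variance to adjust for.

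**3. IMS: how the two definitions differ.** Difference in mean change = difference in mean final score − difference in mean baseline score. The two estimates therefore differ by whatever chance baseline difference exists between the groups, and their standard errors differ too.

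**4. IMS: relative precision.** Let r be the baseline-to-discharge correlation and k = SD(baseline)/SD(final). Neither is given in the article. With the final-score variance set to 1:
- change: 1 + k² − 2rk
- final score adjusted for baseline: 1 − r²

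Assuming equal SDs (k = 1), change becomes 2(1 − r), and adjusted relative to change becomes (1 + r)/2:

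| r (assumed) | Change | Final | Adjusted | Adjusted / change |
|---|---|---|---|---|
| 0.2 | 1.60 | 1.00 | 0.96 | 0.60 |
| 0.3 | 1.40 | 1.00 | 0.91 | 0.65 |
| 0.5 | 1.00 | 1.00 | 0.75 | 0.75 |
| 0.7 | 0.60 | 1.00 | 0.51 | 0.85 |

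Raw change is noisier than the final score only when r is below 0.5, and more precise above it. The adjusted estimate is at least as precise as either, apart from one degree of freedom. If baseline IMS is nearly constant (k near 0), all three coincide.

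**5. Illustration in power.** The article gives no IMS effect. Carrying over the Barthel effect of 13/22 SD (an assumption), with 48 per group and k = 1, power for final / change / adjusted is:
- r = 0.2: 82.5% / 62.9% / 84.0%
- r = 0.5: 82.5% / 82.5% / 91.7%
- r = 0.7: 82.5% / 96.2% / 98.2%

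**6. Cost of leaving the choice open.** With k = 1 and no true effect, the change and final-score test statistics correlate at √[(1 − r)/2], which is 0.63, 0.59 and 0.50 at r = 0.2, 0.3 and 0.5. Reporting whichever is significant at a nominal two-sided 5% gives a false-positive rate of about 8.6%, 8.8% and 9.1%.

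**The case against.** The strongest reply is that this is a one-sentence slip. The abstract and the Aim section point to status at discharge, and the sample size uses a Barthel score. The only scale that was sized gives the same answer either way. Covariates are commonly settled in an analysis plan, which is not at hand. All of that stands, and it limits the point. It does not remove it, because naming the primary variable is the protocol's own task and the IMS is named as a primary endpoint.

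Three stronger readings are tempting, and the article does not support them:
- **That the trial commits to an unadjusted t test of IMS change.** The sentence leading to the t test concerns physiological variables and activity levels, and the final score is named as the endpoint just as plainly as change. What can be said is that no adjustment is stated.
- **That change costs 54% more patients.** That is 1.40/0.91 at an assumed r of 0.3 with equal SDs, comparing change with the adjusted analysis. Against the unadjusted final score, adjustment at the same r is worth about 10% (1/0.91).
- **That omitting ventilation status or age is an error.** Adjusting for them is a preference. Chance imbalance does not invalidate an unadjusted randomized comparison, since its sampling error is already in the confidence interval.

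The spread of baseline IMS is also an inference. Program levels are set by response to commands and muscle strength, not by IMS. An IMS rated for the period before hospitalization would hardly vary among patients who all score 100 on the Barthel Index.

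**Conclusion.** The contradiction is real and sits in consecutive sentences. It is harmless for the Barthel Index and for the sample size, taking baseline as the pre-hospital score, which is the only earlier Barthel assessment described. For the IMS it leaves a named primary endpoint undefined, with two estimators available for reporting.

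The gain from baseline adjustment is conditional on r, on the ratio of SDs and on when baseline IMS is taken, none of which the article states. Under equal SDs and r from 0.2 to 0.7 it ranges from slight to about half of the final-score variance. It is nil if baseline IMS is almost constant. Reconciling the two sentences should be done in any case; the adjustment is a low-cost improvement to a choice the article leaves open, and its absence is not a proven error.

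**What to change.** 1. Delete the sentence defining functional status as a difference. Define the primary endpoint as the score at ICU discharge on each scale, in line with the abstract and the Aim section.
2. State when baseline IMS is recorded. The article collects initial variables after randomization, so specify that the reading precedes the first study session; otherwise it is not a true baseline.
3. Compare discharge IMS between groups with a linear model adjusted for baseline IMS, and keep the unadjusted comparison as a sensitivity analysis. For the Barthel Index, its own baseline offers nothing to adjust for. Further covariates such as ventilation and age are optional; if used, name them in advance.

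The cost is a short amendment or analysis-plan wording, fixed before outcomes are compared by group. Recruitment was still open at publication. No extra patients are needed. No extra measurement is needed either, provided the baseline IMS that the article implies is in fact being recorded; this should be confirmed.

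### The Barthel Index and the IMS are both primary endpoints with no stated success rule, while the sample size rests on the Barthel Index alone

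*Protocol article*

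**What the plan says.** The Methods part of the abstract states: "The primary outcome will be the functional status at ICU discharge, measured with the Barthel Index and the ICU Mobility Scale (IMS"). The section on primary and secondary outcome measures repeats the pairing: "The functional status is the difference between baseline and final score on both the Barthel Index and the IMS". It then uses the plural, so that "the quantitative final score on those scales will be considered as the primary endpoints of the study". Neither place forms a composite, sets an order, or says what pattern of results on the two scales would count as success.

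The section on statistical analysis and sample size speaks of one primary outcome. The trial is sized for a "difference in means in the primary outcome (Barthel Index score) of 13 points and a standard deviation of 22 points". The error rates come from a single statement, "Considering a statistical power of 80% and an alpha error of 0.5", and the result is that "the number of subjects should be 48 per group, totaling 96 patients in the study". That section also says that the groups will be compared on all outcome variables. No expected difference, standard deviation or power is given for the IMS anywhere in the article.

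**The concern.** Two parts of the article describe two primary endpoints and a third sizes the trial for one. The missing link is the success rule, which determines both the type I error of the primary claim and the number of patients needed.

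The practical risk is a split result, with one scale significant and the other not. The article gives no prespecified reading of that outcome, so the superiority claim could come to rest on whichever scale looked favourable. If either scale were allowed to carry the claim at the full level, the false-positive rate would exceed the nominal one. If alpha were divided to prevent this, the Barthel comparison would fall short of its planned power. If both scales had to succeed, the planned power would refer to only half of the claim.

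**Working it through.** **Inputs from the article (statistical analysis and sample size section).** Barthel difference 13, SD 22, so d = 13/22 = 0.591; power 80%; 48 per group, 96 in total.

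**Assumptions.** Alpha is two-sided 0.05: the article prints 0.5, which looks like a misprint, and gives no sidedness. The correlation between the two test statistics and the IMS effect are not given, so ranges are shown.

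**1. The plan's own figure.** Normal approximation: n per group = 2 × (SD/difference)² × (z for alpha + z for power)².
- Alpha 0.5 two-sided, as printed: 13.2, so 14 per group. This does not reproduce 48.
- Alpha 0.05 two-sided: 2 × (22/13)² × (1.960 + 0.842)² = 44.96, so 45 per group (90). The t test needs 46 per group (92).
- Alpha 0.05 one-sided: 36 per group (72).

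The stated 48 is therefore slightly generous for the Barthel Index alone at two-sided 0.05. Power at 48 per group is 81.7% by the t test and 82.5% by the normal approximation: Φ(0.591 × √24 − 1.960) = Φ(0.935).

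**2. If either scale sufficed, each tested at 0.05.** Family-wise error = 1 − P(|Z1| < 1.96 and |Z2| < 1.96), with Z1 and Z2 bivariate normal.

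| Correlation | Family-wise error |
|---|---|
| 0 | 9.75% |
| 0.5 | 9.1% |
| 0.8 | 7.8% |
| 0.9 | 7.0% |

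**3. If either scale sufficed, with a Bonferroni split (0.025 each).** Barthel power at 48 per group falls from 81.7% to 73.1% (t test). Restoring 80% needs 56 per group (112) by the t test, or 55 (110) by the normal approximation.

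**4. If both scales had to succeed, each at 0.05.** No alpha adjustment is needed. Joint power = P(Z1 > 1.96 and Z2 > 1.96), with means d × √(48/2) for each scale (normal approximation). With an IMS effect equal to the Barthel effect (0.591):

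| Correlation | Joint power at 48 per group | Per group for 80% |
|---|---|---|
| 0 | 68% | 60 (120 in total) |
| 0.5 | 72% | 57 (114) |
| 0.9 | 78% | 51 (102) |

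A larger IMS effect changes the answer. At d = 0.85 and correlation 0, joint power is 0.825 × 0.986 = 81%.

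**5. If the Barthel Index is the sole primary endpoint, or is tested first.** The Barthel test keeps the full 0.05 and its 81.7% power at 48 per group. No increase is needed.

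**The case against.** The strongest reply is that this is a condensed article and that a multiplicity method or testing order is commonly placed in an analysis plan that is not shown. That is fair as far as it goes: the article's silence on multiplicity does not show that the trial has no error control, and the point does not rest on that silence. What stands is that this document itself names two primary endpoints in two places and powers one in a third. The choice of success rule also bears on the 48 per group that the article has already fixed.

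A second reply is that the Barthel score in parentheses may only identify the measure used for sizing, which would make the sample size section incomplete rather than contradictory. That reading is possible. It still leaves the IMS as a primary endpoint with no design assumptions behind it.

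A reader might infer three stronger things that the article does not support:
- That both scales will be tested at the full level. The article gives one alpha, in the sample size paragraph, and assigns no level to the IMS test.
- That the type I error is inflated. This follows only if either scale suffices, a rule that the article never states. Requiring both inflates nothing.
- That 80% power must fail if both scales are required. It depends on an IMS effect that is not given, and a large enough effect would meet the target.

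Independence of the two scales is also the least plausible case for two functional measures taken on the same patients at the same time, so 9.75% is an upper end and not a central estimate.

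**Conclusion.** The point holds as a mismatch within the article: two primary endpoints without a success rule, and a sample size that supports one. The size of the consequence depends on which rule is meant. It is a family-wise error of about 7.0% to 9.75% if either scale counts at 0.05; Barthel power of 73.1% instead of 81.7% if alpha is split; joint power of about 68% to 78% if both are required and the IMS effect equals the Barthel effect; and no loss if the Barthel Index stands alone or is tested first. Only this last reading is fully supported by 96 patients on the figures given, and the outcome section does not state it. All of these figures assume two-sided 0.05, and the ranges cover correlations from 0 to 0.9. The printed alpha of 0.5 and the small surplus of 48 over 46 per group are separate matters and do not alter the conclusion.

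Because the gap concerns what would count as a positive trial, it should be closed before outcomes are compared by group.

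**What to change.** Bring the abstract, the outcome section and the sample size section into agreement. Name the Barthel Index at ICU discharge as the single primary endpoint, as the sample size already implies. Make the IMS the first key secondary endpoint, tested at two-sided 0.05 only if the Barthel result is significant at two-sided 0.05. This fixed sequence holds the error across the two tests at 5% and keeps Barthel power at 81.7% with 48 per group.

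The article reports recruitment as under way, so the change should be made and dated before any comparison of outcomes by group.

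The cost is an amendment, with the registry entry brought into line if it differs. No extra patients are needed. The real concession is that a significant IMS result alone can no longer carry the primary claim. If the investigators want the IMS to keep primary status, a split alpha or a requirement for both scales would also settle the rule, but the sample size would then have to be justified again: 56 per group for the Bonferroni split, or a stated IMS effect and SD for the joint requirement.
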